#### Data protection

2.18.1

All procedures comply with the Kenya Data Protection Act (2019) and General Data Protection Regulation (GDPR) (34) aligned principles of confidentiality, integrity, and lawful processing.

Participants will be identified only by unique study codes. Research and facility data will be stored separately, ensuring full anonymization prior to analysis.

#### Data quality

2.18.2

Data quality will be maintained through electronic validation checks, routine consistency reviews, periodic audits, and standardized operating procedures. Data quality monitoring will follow International Council for Harmonisation Good Clinical Practice (35) guidelines.

##### Documentation and metadata (FAIR principles)

2.18.2.1

Study documentation, metadata, and analysis scripts will comply with FAIR (Findable, Accessible, Interoperable, and Reusable) data principles (30).

#### Data analysis plan

2.18.3

Data analysis will follow an intention-to-treat (ITT) approach (36).

Analytical methods will include:

Descriptive statisticsChi-square tests (55)McNemar’s and Cochran’s *Q* tests (22, 58)Logistic regression (37)Thematic qualitative analysisCost-effectiveness analysis (38)

#### Data sharing

2.18.4

De-identified datasets and analysis scripts will be preserved and shared in accordance with FAIR principles. Data will be deposited at the Kenya Medical Research Institute (KEMRI) and or Jomo Kenyatta University of Agriculture and Technology (JKUAT) Institutional Repositories and retained for a minimum of 10 years.

#### Responsibility

2.18.5

The Principal Investigator (PI) will have overall responsibility for data governance and oversight (49).

### Statistical analysis

2.19

All analyses will follow a prespecified Statistical Analysis Plan (SAP) deposited with the PACTR registry. Analyses will be conducted under an intention-to-treat framework to preserve randomization integrity (36).

A two sided significance level of 0.05 will be used throughout, with 95% confidence intervals reported (48).

#### Primary analysis

2.19.1

The primary outcome will be analyzed using generalized linear mixed effects models (GLMMs) with a link to compare HIV testing uptake between study arms over time while accounting for within participant correlation.

Fixed effects will include:

Study armFollow up timeArm × time interaction

Random intercepts will account for repeated observations within participants.

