### Sample size determination

2.8

The primary outcome of this trial is HIV testing uptake, defined as completion of at least one HIV test during the study period. Because the primary outcome is binary and reported as a population proportion, the sample size was estimated using Cochran’s formula for proportions (22).

$$n0=(Z^{2}\cdot p\cdot q)/e^{2}$$

Where *Z* represents the critical value for a 95% confidence level (1.96), *e* denotes the acceptable margin of error (0.05), and p represents the estimated baseline proportion of HIV testing uptake. Given that the true HIV testing prevalence within this online male demographic was undetermined, *p* was conservatively set at 0.50 (*q* = 1 − *p* = 0.50) to assume maximum population variance and yield the most conservative sample size baseline. This primary calculation established a baseline requirement of 384 participants. To account for anticipated digital non-response and loss to follow-up, an approximate 22% attrition adjustment was applied (inflating the sample via *n* = *n*₀/0.82), resulting in a final cleared sample size of 468 participants allocated equally across the three study arms in a 1:1:1 ratio (156 participants per arm). Within each arm, participants will be stratified by age group prior to simple randomization to preserve developmental balance.

To validate this allocation against the primary objective, a supplementary power assessment was conducted using the standard formula for comparing two independent proportions:

$$n=[{\left(Z\_\{\alpha /2\}+Z\_\beta \right)}^{2}\cdot (p₁(1-p₁)+p₂(1-p₂))]/{\left(p₁-p₂\right)}^{2}$$

Where *α* is fixed at a two-sided significance level of 0.05 (*Z*_{*α*/2} = 1.96) and statistical power is fixed at 80% (*Z*_*β* = 0.84). Based on evidence highlighting depressed health seeking behaviors among young men in Kenya alongside historical peer led intervention data demonstrating up to 50% relative increases in testing uptake within sub-Saharan Africa, the calculation assumed an expected HIV testing uptake rate of 20% (*p*₁) in the active control arm and 40% (*p*₂) in the intervention arms (15, 16). This establishes an estimated absolute effect size of 20 percentage points.

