### Stratification, randomization and allocation

2.9

Following consent and baseline assessment, participants will be stratified into three prespecified age groups:

*Stratum A*: 18–22 years (Young Gen Z)*Stratum B*: 23–27 years (Older Gen Z)*Stratum C*: 28–32 years (Young Millennials)

This stratification approach is informed by evidence demonstrating age related differences in HIV testing uptake and health seeking behaviors among young men (24), as well as variation in peer influence within social networks (25).

Each stratum will include 156 participants, with equal allocation across study arms (52 participants per arm per stratum), yielding a total sample size of 468 participants.

Within each stratum, participants will be randomly assigned in a 1:1:1 ratio using computer generated block randomization with a fixed block size of six. Randomization sequences will be prepared independently before recruitment by an independent randomization officer not involved in enrolment.

Allocation concealment will be maintained using centralized password-protected computerized randomization. Recruitment staff will remain unaware of future allocations until assignment has occurred (see Figures 1, 2).

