### Data collection

2.17

Data for this study will be collected using a fully digital, longitudinal approach aligned with the hybrid trial design, integrating repeated measures, online platform derived engagement data, and anonymized facility based verification (52, 57).

Data collection procedures are prespecified in the study Data Management Plan (DMP; DMPTool Registry No.10.48321D1D8C7728A), ensuring transparency and reproducibility (30). Data will be collected at baseline (Week 0) and during follow up assessments at Weeks 2, 6, 10, and 12 using standardized electronic data collection instruments.

Baseline data will include demographic characteristics, socioeconomic characteristics, HIV testing history, HIV related knowledge, digital media use, and other variables relevant to the study objectives.

Follow up assessments will capture intervention exposure, participant engagement, HIV testing behavior since the previous assessment, linkage to care, adverse events, and protocol deviations.

All questionnaires will be completed electronically through secure online platforms using standardized instruments across all study arms.

Intervention engagement will be monitored using WhatsApp platform metrics, including message delivery, read status, participant responses, and interaction frequency to assess intervention fidelity.

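### Randomisation is stratified by age, but the primary model's listed fixed effects leave age stratum out; if age is prognostic, the test is mildly conservative

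*Protocol article*

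**What the plan says.** Section 2.9 of the protocol article (Stratification, randomization and allocation) states that "participants will be stratified into three prespecified age groups": 18–22, 23–27 and 28–32 years. The reason given is that "This stratification approach is informed by evidence demonstrating age related differences in HIV testing uptake". Allocation is 1:1:1 inside each stratum by "computer generated block randomization with a fixed block size of six", with 52 men per arm per stratum.

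Section 2.19.1 (Primary analysis) specifies a generalized linear mixed model with a participant random intercept. Its fixed effects are listed as "Study armFollow up timeArm × time interaction" (three items that run together in the extracted text). Age stratum is not among them. Section 2.19.2 places multivariable logistic regression and age-stratified subgroup analyses among the secondary analyses.

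Section 2.17 says "Baseline data will include demographic characteristics, socioeconomic characteristics, HIV testing history", and section 2.17.3 repeats testing history in the baseline list. The primary model does not name it either.

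Section 2.8 (Sample size determination) describes the allocation differently: "Within each arm, participants will be stratified by age group prior to simple randomization to preserve developmental balance".

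**The concern.** The protocol treats age as prognostic for the primary outcome and builds the randomisation around it. Blocking within stratum makes the arms alike in age, which removes between-stratum variation from the arm comparison. A model without stratum does not credit that balance. The larger the age differences in uptake, the further the actual type I error falls below 5%, and the more power is given up. What is at stake is efficiency and an analysis that follows the design, not protection against false positives.

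The sample-size sentence raises a second, separate matter. Stratifying inside arms cannot come before randomisation, because arms do not exist until men are randomised, and simple randomisation is a different procedure from permuted blocks.

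**Working it through.** **1. The plan's own figures.** Section 2.8: 1.96² × 0.5 × 0.5 / 0.05² = 384.16, stated as 384; 384 / 0.82 = 468.3, stated as 468. For 20% versus 40%, the printed two-proportion formula gives (1.96 + 0.84)² × (0.2 × 0.8 + 0.4 × 0.6) / 0.2² = 7.84 × 0.40 / 0.04 = 78.4, so 79 per arm against 156 planned. Power at 156 per arm is 97.4%. No input to these calculations involves a covariate, so adding one leaves the sample size unchanged.

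**2. Allocation method.** 52 × 3 arms × 3 strata = 468, and 156 / 6 = 26 complete blocks per stratum, so section 2.9 is internally consistent. Under simple 1:1:1 randomisation of 156 men, an arm's count has standard deviation √(156 × 1/3 × 2/3) = 5.9, so counts of about 40 to 64 would be ordinary. The chance of exactly 52/52/52 in one stratum is 156! / (52!)³ / 3¹⁵⁶ ≈ 0.5%. Only the blocks of section 2.9 deliver the stated cells.

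**3. Why the unadjusted test is conservative.** On the risk-difference scale under the null, the usual two-group variance is proportional to p̄(1 − p̄). With exact balance by stratum, the contrast actually varies in proportion to p̄(1 − p̄) − Var(pₛ), where pₛ is uptake in stratum s. Put r = Var(pₛ) / [p̄(1 − p̄)]. The true two-sided error is then that of a normal variable beyond 1.96 / √(1 − r).

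- 15/20/25%: r = 0.00167 / 0.16 = 1.0%; cut-off 1.970; error 0.049.
- 10/20/30%: r = 0.00667 / 0.16 = 4.2%; cut-off 2.002; error 0.045.
- 5/20/40%: p̄ = 0.2167, r = 0.0206 / 0.1697 = 12.1%; cut-off 2.091; error 0.037.

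**4. Simulation.** One pairwise comparison, 52 men per arm per stratum, a single binary endpoint, Wald test from logistic regression, no attrition. It approximates the planned mixed model and does not reproduce it. The stratum uptakes are assumptions. The treatment effect is a constant odds ratio of (0.4/0.6) / (0.2/0.8) = 2.67, so 20% versus 40% holds exactly in a stratum with 20% control uptake. Overall, the difference is 20.0, 19.7, 18.7 and 17.1 points in the four rows. The rows should therefore be read across, not down.

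| Control uptake by stratum | Type I error, unadjusted / age-adjusted | Power 20% vs 40%, unadjusted / age-adjusted |
|---|---|---|
| 20/20/20% | 0.052 / 0.053 | 97.4 / 97.5% |
| 15/20/25% | 0.044 / 0.046 | 97.1 / 97.3% |
| 10/20/30% | 0.042 / 0.047 | 95.4 / 96.0% |
| 5/20/40% | 0.029 / 0.046 | 94.0 / 95.7% |

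There were 3,000 runs for type I error (Monte Carlo standard error about √(0.05 × 0.95 / 3000) = 0.004) and 1,500 for power (about 0.5 points at 96%). Both methods were applied to the same simulated data. The simulated errors follow the direction of step 3. For a smaller effect, 20% versus 35% in the middle stratum (3,000 runs), the power pairs are 85.5/85.8, 83.5/83.8, 82.0/83.4 and 75.7/80.3%, so the loss reaches 4.6 points only at the widest spread.

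**5. Testing history.** Here it is assumed that half the men have a positive history and that its odds ratio for testing is 3. Power for 20% versus 40% (unadjusted / age / age and history) is then 93.9 / 94.8 / 96.1% at 10/20/30% and 90.3 / 93.7 / 94.1% at 5/20/40%. Leaving out both costs up to about 4 points under these assumptions.

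**The case against.** The strongest reply is that the model may not be final. Section 2.19.1 says what the fixed effects will include, which need not be exhaustive, and section 2.19 refers to a statistical analysis plan that is not shown here. An article may leave adjustment covariates to that plan. This stands in part: the document nowhere declares the primary analysis unadjusted, and the plan may already contain the stratum. But the protocol does not defer the model terms. It writes them out, down to the interaction, and omits the one factor on which allocation is balanced. If the plan does adjust, the published model still needs the term.

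The second reply is that the effect is small, and this stands. Planned numbers are about twice what 20% versus 40% requires, and if uptake hardly differs by age the gain is close to nil.

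Third, testing history is not a stratification factor, and nothing in the document requires adjustment for it. That stands too: its absence is a lost chance of efficiency, not an error. The document does not show that recency of testing is recorded, so a covariate such as a test in the past 12 months cannot be presumed available.

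Fourth, the sample-size wording is editorial. Section 2.9 is the dedicated section, and the Figure 2 caption also describes stratified blocks. The contradiction is real, but it adds no weight to the point about the model.

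**Conclusion.** The point holds as a modest one. The primary model as listed does not include the age strata by which the trial randomises. Under assumed control uptake from no difference to 5/20/40%, the unadjusted type I error lies between about nominal and about 0.03, and omitting age costs about 0 to 2 points of power for 20% versus 40%. These figures rest on assumed stratum uptakes, a single binary endpoint and full follow-up.

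A reader might infer three stronger things that the documents do not support:

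- **Invalid or inflated false positives.** The error is in the conservative direction, and planned power for a 20-point difference is not threatened.
- **A smaller standard error from adjustment.** The variance argument in step 3 of the working is on the risk-difference scale. In a logistic model, adding a prognostic covariate does not in general shrink the standard error of the log odds ratio; the test gains because the conditional effect lies further from the null.
- **A saving equal to a stated number of participants.** The protocol gives no uptake by age or by testing history from which to calculate one.

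**What to change.** - **Section 2.19.1:** add age stratum (three levels) as a fixed effect in the primary model. If the statistical analysis plan already has it, state so in the protocol.
- **Optional:** prespecify baseline HIV testing history, in the form in which it is collected, as a further covariate for efficiency, noting that the gain depends on how strongly it predicts testing.
- **Reporting:** because adjustment changes the conditional odds ratio, a standardised risk difference can be reported alongside it.
- **Section 2.8:** replace the sentence on stratification within arms and simple randomisation with the method of section 2.9, permuted blocks of six within age stratum.

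The cost is one model term, a second if testing history is added, and one corrected sentence. No new data are needed and the sample size does not change. The model should be settled before the analysts' treatment codes are unmasked.

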### Study design

2.1

This study is a three arm, parallel group, age stratified; randomized controlled trial (RCT) with equal allocation (1:1:1) will be conducted over a 12 week period. The trial compares the effectiveness of three different HIV testing uptake promotion strategies of increasing intensity: Arm 1 (active control), Arm 2 (comparator), or Arm 3 (intervention). Participants will be followed for 12 weeks, with outcome assessments at baseline (0) and weeks 2, 6, 10, and 12 using a repeated measures framework (17, 18, 56).

Consistent with the parallel group design framework established by Schulz et al. (18), the three different study arms (WhatsApp groups) will each concurrently receive different interventions promoting HIV testing uptake during the 12 week study period.

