### Intervention Arms

2.10

Participants will be randomly allocated to one of three intervention arms of increasing intervention intensity.

*Arm 1 (active control)*: participants will receive routine HIV promotion messages broadcast through the partner FM radio station.

*Arm 2 (standard digital messaging)*: participants will receive the FM radio intervention together with standardized HIV related WhatsApp messages delivered through closed WhatsApp study group.

*Arm 3 (peer influencer intervention)*: participants will receive the FM radio intervention, standardized WhatsApp messaging, and additional engagement from trained online peer influencers who will facilitate discussions, share structured HIV testing messages, provide behavioral prompts and reminders, answer general questions, and encourage HIV testing at the partner HIV Testing Services (HTS) facility.

Interventions will be delivered over a 12-week period.

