### Online peer influencer intervention

2.11

A total of 15 online peer influencers (five per age stratum) will be identified using social network analysis (SNA) methods. This approach enables objective selection of individuals with high influence within digital networks, improving intervention reach and effectiveness compared to convenience-based peer educator models (25).

Peer influencers will complete standardized virtual training covering HIV communication, ethical conduct, participant engagement, confidentiality, and referral procedures. Throughout the intervention they will receive ongoing supervision, weekly monitoring, and fidelity assessments.

Peer influencers will facilitate WhatsApp discussions, encourage HIV testing, distribute referral information, and support participant engagement. They will not participate in recruitment, randomization, outcome assessment, or data analysis (44).

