### Contamination prevention

2.12

To minimize contamination, each study arm will operate within separate closed WhatsApp groups. Participants will have no interaction across study arms, and peer influencers will communicate only with participants assigned to their respective intervention group.

Potential contamination will be assessed during process evaluation (26).

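### Arms 2 and 3 are delivered in WhatsApp groups, but the primary model and the sample size treat men as independent; if outcomes correlate within groups, standard errors are too small

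*Protocol article*

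**What the plan says.** Section 2.9 randomises individual men within age strata, with 52 men per arm per stratum and 156 per arm.

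Delivery is by group. In section 2.10, Arm 2 receives "standardized HIV related WhatsApp messages delivered through closed WhatsApp study group", and Arm 3 adds "additional engagement from trained online peer influencers who will facilitate discussions". Section 2.11 sets the number of influencers: "A total of 15 online peer influencers (five per age stratum"). The number and size of the WhatsApp groups, and how men are attached to influencers, are not given.

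Section 2.19.1 specifies the primary model as a generalized linear mixed model "to compare HIV testing uptake between study arms over time while accounting for within participant correlation". The fixed effects are arm, time and their interaction. The random part is: "Random intercepts will account for repeated observations within participants". Section 2.8 sizes the trial with formulas for independent observations. The article mentions no group or influencer term, cluster-robust variance, ICC or design effect.

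On Arm 1 the protocol differs from itself. Section 2.10 says only that "participants will receive routine HIV promotion messages broadcast through the partner FM radio station". Section 2.12 says "each study arm will operate within separate closed WhatsApp groups", and section 2.1 says "the three different study arms (WhatsApp groups) will each concurrently receive different interventions".

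**The concern.** This is an individually randomised trial with group-delivered treatment. Men in an Arm 3 group share the same discussion and the same influencers, and one man acting on what others say is how the intervention is meant to work. Outcomes in a group may therefore move together.

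A participant random intercept does not deal with this. It takes up variation between groups as if it were variation between men, and still counts the men as independent. With positive within-group correlation, the standard error of the arm effect is too small, confidence intervals are too narrow, and the nominal 5% test rejects too often.

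The stated objective, the added value of influencers over radio plus WhatsApp, is the Arm 3 v Arm 2 contrast. Both of those arms are delivered through groups. If each arm were one group, the effect of that group could not be told apart from the effect of the arm.

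**Working it through.** **The plan's own figures (section 2.8).** They reproduce under independence.
- Cochran: 1.96² × 0.25 / 0.05² = 384.2. Then 384 / 0.82 = 468.3, and 468 / 3 = 156 per arm.
- Two proportions: (1.96 + 0.84)² × (0.16 + 0.24) / 0.20² = 78.4 per arm, well below 156.
- Power with the same unpooled variance: at 156 per arm, 0.2 / √(0.4/156) = 3.95 and Φ(3.95 − 1.96) = 97.7%. At 128 per arm (384 / 3, after attrition), 0.2 / √(0.4/128) = 3.58 and Φ(3.58 − 1.96) = 94.7%.

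**Inputs that the documents do not give.**
- ICC: assumed 0.01, 0.02 and 0.05.
- Group size m: 156 / 15 = 10.4 if each influencer has his own men; 52 if there is one group per arm and stratum.

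**Type I error.** The design effect is DE = 1 + (m − 1) × ICC. Under the null hypothesis the true variance of the contrast, relative to the model's, is (1 + DE)/2 when only one arm is clustered and DE when both are equally clustered. The true type I error is 2 × [1 − Φ(1.96 / √ratio)].

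| m | ICC | DE | One arm clustered (Arm 3 v Arm 1) | Both equally clustered (Arm 3 v Arm 2) |
|---|---|---|---|---|
| 10.4 | 0.01 | 1.09 | 5.5% | 6.1% |
| 10.4 | 0.02 | 1.19 | 6.1% | 7.2% |
| 10.4 | 0.05 | 1.47 | 7.8% | 10.6% |
| 52 | 0.01 | 1.51 | 8.0% | 11.1% |
| 52 | 0.02 | 2.02 | 11.1% | 16.8% |
| 52 | 0.05 | 3.55 | 19.4% | 29.8% |

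The Arm 3 v Arm 1 column takes Arm 1 as unclustered. If Arm 2 outcomes are not correlated within group, Arm 3 v Arm 2 also follows that column. At ICC 0, DE = 1 and the error is 5% throughout.

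**Power, Arm 3 v Arm 1, 20% v 40%, 128 per arm.** Power = Φ(0.2 / √[(0.16 + 0.24 × DE)/128] − 1.96). Group sizes are reduced by the same attrition: 128 / 15 = 8.5 and 128 / 3 = 42.7.

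| m | ICC 0.01 | ICC 0.02 | ICC 0.05 |
|---|---|---|---|
| 8.5 | 94% | 93% | 90% |
| 42.7 | 89% | 83% | 66% |

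If the small groups are held at 10.4, the value at ICC 0.05 is 89%.

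**One group per arm.** With m = 156, the same formulas give 14-37% (one arm clustered) and 22-51% (both). These figures are only illustrative, because no analysis can estimate a group variance from one group.

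All of this is a normal approximation for a single comparison of proportions, not a simulation of the repeated-measures model.

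**The case against.** **The ICC is unknown.** This stands. A reader might infer that the standard errors are certainly too small. The documents support only a conditional statement: correlation is plausible from the stated mechanism, but it is not quantified.

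**Arm 2 may not be clustered.** Section 2.10 describes standardized messages for Arm 2; facilitated discussion appears only for Arm 3. This stands too. The 6-11% and 11-30% figures need equal clustering in both arms and are the upper case.

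**The powered contrast is the one less affected.** Section 2.8 says the trial is not powered for a definitive comparison of the two WhatsApp arms. That is so, but the stated objective is that comparison, and an interval that is too narrow misleads whatever the power.

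**Power is lost.** A reader might infer this as well. It is mostly not so: the 156 per arm leaves ample slack over the 78.4 required, and at the two group sizes examined power falls below 80% only with large groups and the highest ICC.

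**The control arm gets a peer group.** The conflicting text on Arm 1 could be read this way. The documents do not establish it: section 2.4.4 runs enrolment and follow-up through WhatsApp, so an Arm 1 group might be purely administrative.

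**The SAP is not shown and the article is condensed.** A further random effect could be specified there. But section 2.19.1 does state which correlation the model addresses and which random effect it uses, and section 2.8 does state the sample size basis. The point is about what is stated.

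**Conclusion.** The point holds in conditional form. As written, the primary model does not account for correlation within WhatsApp group or influencer. If that correlation is positive, p-values and intervals for contrasts involving a clustered arm are anti-conservative.

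The effect is slight with groups of about 10 and a low ICC, and substantial with groups of 52. The size rests on the assumed ICC range, on the two assumed group sizes, and, for Arm 3 v Arm 2, on whether Arm 2 is clustered. The main issue is the validity of the inference; loss of power is secondary. The Arm 1 descriptions contradict each other and need reconciling, because they decide the nesting structure and what the control condition is.

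**What to change.** 1. Record the WhatsApp group and the influencer for each man.
2. Add a group-level random effect, or a cluster-robust variance, for the group-delivered arms. Use a partially nested form in which men in no group stand alone, with small-sample degrees of freedom.
3. Restate power over a range of ICCs and for the planned group size.
4. State the number of groups, with more than one in each WhatsApp arm. With only three per arm the group variance is poorly estimated, so more groups are better for the analysis. If delivery stays at one group per arm, state that the group effect cannot be separated from the arm effect and that this limits the conclusion.
5. Reconcile section 2.10 with sections 2.1 and 2.12 on whether Arm 1 has a WhatsApp group and, if so, what it is for.

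Items 1, 2, 3 and 5 cost two identifier variables, one model term and some text, with no extra participants. The price is wider intervals and somewhat lower stated power. Item 4 may cost more: dividing an arm into many small groups could change how the intervention is delivered, so it should be decided before the groups are formed, since it cannot be repaired afterwards.
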